## Abstract

**Background:**

Parkinson's Disease is a degenerative neurological condition that causes movement problems and other distressing symptoms. People with Parkinson's disease gradually lose their independence and strain is placed on family members. A multidisciplinary approach to rehabilitation for people with Parkinson's is recommended but has not been widely researched. Studies are needed that investigate cost-effective community-based service delivery models to reduce disability and dependency and admission to long term care, and improve quality of life.

**Methods:**

A pragmatic three parallel group randomised controlled trial involving people with Parkinson's Disease and live-in carers (family friends or paid carers), and comparing: management by a specialist multidisciplinary team for six weeks, according to a care plan agreed between the professionals and the patient and carer (Group A); multidisciplinary team management and additional support for four months from a trained care assistant (Group B); usual care, no coordinated team care planning or ongoing support (Group C). Follow up will be for six months to determine the impact and relative cost-effectiveness of the two interventions, compared to usual care. The primary outcomes are disability (patients) and strain (carers). Secondary outcomes include patient mobility, falls, speech, pain, self efficacy, health and social care use; carer general health; patient and carer social functioning, psychological wellbeing, health related quality of life. Semi structured interviews will be undertaken with providers (team members, care assistants), service commissioners, and patients and carers in groups A and B, to gain feedback about the acceptability of the interventions. A cost - effectiveness evaluation is embedded in the trial.

**Discussion:**

The trial investigates components of recent national policy recommendations for people with long term conditions, and Parkinson's Disease in particular, and will provide guidance to inform local service planning and commissioning.

**Trial registration:**

ISRCTN: ISRCTN44577970

## Background

Parkinson's disease is a degenerative neurological condition that affects mainly older people, but also significant numbers with young onset [1]. Although designated a movement disorder, it additionally inflicts a range of distressing non motor symptoms. As the disease progresses, people with Parkinson's become increasingly dependent and a considerable burden is carried by family carers. The mainstay of management is a pharmacological regimen which gradually becomes less effective, and more complicated. This is supported by rehabilitative therapies, assistive technologies and occasionally surgery. A multidisciplinary team (MDT) approach to rehabilitation is accepted best-practice [2-4], but has not been widely researched [4-7]. Whilst a self management programme has been found to have positive effects on health-related quality of life at six months [8], other community-based studies have only measured immediate outcomes [9,10], or found no longer term benefits [11]. A need has been expressed for studies that identify cost-effective service delivery models that reduce disability and dependency and prevent admission to long term care [3-7].

The SPIRiTT study (Specialist Parkinson's Integrated Rehabilitation Team Trial) builds on the findings of a previous multidisciplinary rehabilitation programme, coordinated by a Parkinson's Nurse Specialist (PNS) in a day hospital setting [12]. This intervention resulted in significant immediate gains for patients in mobility, independence, wellbeing and health-related quality of life [10], but, in the absence of continuing input, these benefits had largely dissipated four months after the intervention ended [12]. Moreover, the accompanying economic evaluation showed that day hospital treatment incurred facility overhead costs and involved the use of expensive hospital transport for patients with more advanced disease who were unable to make their own arrangements [13]. SPIRiTT specifically addresses the issue of patient transport raised by the day hospital model by delivering rehabilitation to people in their own homes. Moreover, it evaluates whether the fading of benefit when specialist input is withdrawn, (a common feature of time limited rehabilitation interventions [5]), can be avoided in a cost - effective way by providing continuing support from specially trained care assistants. Participants in SPIRiTT will receive an equivalent package of specialist rehabilitation to that used in the day hospital study so that valid comparisons can be drawn between the models of domiciliary and day hospital provision.

The SPIRiTT model of service delivery is grounded in the recommendations of several recent policy documents of the English National Health Service (NHS). These promote: the integration of health and social care services [14], provision of services closer to patients' homes [14], coordination of care for particular patient groups by specialist disease-specific nurses [15], supported self management [15], and personalised care planning, rehabilitation and carer support in order to reduce costly unplanned hospital admissions [16]. Moreover, guidelines from the National Institute for Health and Clinical Excellence (NICE) for the management of Parkinson's disease [3] recommend regular patient review, comprehensive care plans, a central role for PNS and regular access to physiotherapy, occupational therapy and speech and language therapy.

Many people with Parkinson's do not currently see individual therapists and even fewer receive coordinated MDT input [17,18]. SPIRiTT will investigate the cost-effectiveness of implementing a proactive approach to Parkinson's management, in line with recent recommendations. Other research has shown routine assessment and support for older people living in the community with a variety of conditions can have positive effects on mortality and admission to long term care [19]. Evaluations have been conducted in a range of countries, including the United States [20-23], Canada [24], Australia [25,26], Denmark [27,28], Italy [29] and Switzerland [30], but overall evidence on outcomes (such as physical functioning and health-related quality of life), service use and costs is inconsistent [26,31]. The findings from SPIRiTT will extend the current evidence base through a focus on outcomes for people with Parkinson's.

Capacity constraints in the form of high nurse caseloads and shortages of therapists were identified by NICE as barriers to the delivery of their guidance for management of Parkinson's disease [3], and these have been confirmed by a recent survey of PNS [32]. Whilst NICE recommends a caseload of 300 patients, over half of PNS have lists in excess of 500, with adverse effects on the amount of routine support they can provide to patients. In common with other advanced practice nurses in the community, PNS report undertaking a variety of tasks (some of which do not require advanced skills), and that time pressures create a need to risk stratify patients, and a focus on 'crisis' management, rather than ongoing advice and support [33,34]. Use of care assistants, trained in the special features and management of Parkinson's, working with PNS and multidisciplinary teams of healthcare professionals in the community on assigned tasks appropriate to their skill level and knowledge, is one way in which resources for delivering care and support to people with Parkinson's can be increased.

Competency-based training enables non registered staff to properly complement the activities of professionals [14,35], and professionals to appropriately meet supervision, delegation and accountability challenges [36]. Trained care assistants have been shown to be effective at underpinning professional working and to have a positive impact on nurse's ability to provide high quality care, their work experiences, and the cost-effectiveness of service delivery [37]. The use of trained assistants is consistent with NHS policy for the health and social care workforce which advocates the integration of non registered health and social care workers with enhanced roles in MDTs, to implement and deliver therapy and monitor and support patients [16,38], as a means of increasing the flexibility, efficiency and responsiveness of services [39,40].

The **aims **of the SPIRiTT study are to evaluate two models of specialist MDT rehabilitation for people with Parkinson's in the community, to add to the existing evidence base, to inform future service development and commissioning, and ultimately to improve the quality of care and outcomes for patients and family carers. The specialist intervention is based on a rehabilitation service that works with the patient and family to resolve problems, through a process of goal setting, care planning, intervention and evaluation, to achieve outcomes that maximize functioning and social participation with minimum distress to patient or family carer [41]. The research will explore not just the multidisciplinary professional input, but also budgetary and management arrangements, and barriers and facilitators to cross sector working, that may impact on future implementation of the model.

The specific **objectives **are to:

1. Implement a specialist neurological rehabilitation service for people with Parkinson's and their family carers, delivered in their own homes, comprising MDT assessment, care planning and treatment (following the protocol previously evaluated in a day hospital setting);

2. Provide ongoing support from specially trained care assistants to half (randomly selected) of those receiving the specialist rehabilitation;

3. Evaluate the clinical effectiveness of the specialist rehabilitation service, and the value added by ongoing support from trained care assistants embedded in the MDT, compared to usual care, (which is largely non specialist and non team based), across a range of patient and carer outcomes;

4. Assess the costs of the specialist rehabilitation intervention, and of the ongoing care assistant support, and calculate relative cost-effectiveness, including consideration of savings from service use offsets;

5. Investigate the acceptability of the new service delivery models (specialist domiciliary rehabilitation with and without ongoing support from trained care assistants) from the perspectives of all stakeholders including commissioners, MDT members, care assistants, service managers, patients and family carers;

6. Deliver guidance for commissioners, providers and policy makers about the acceptability, clinical and cost-effectiveness of different models of specialist neurological rehabilitation.

The **hypotheses **are that:

1. A package of domiciliary multidisciplinary specialist rehabilitation will benefit:

a. People with Parkinson's in terms of maintaining mobility and independence (primary outcome for patients), and improving wellbeing and health-related quality of life,

b. Family carers in terms of reduced strain (primary outcome for carers), and improved health-related quality of life, and

c. Society through reduced use of other health and social care services, including hospitalisations and admissions to long term care.

2. The addition of four months of ongoing support from trained care assistants will help to maintain the benefits of the specialist team rehabilitation, and avoid the fading of effects that typically accompanies the withdrawal of input.

3. The intervention will be acceptable to major stakeholders, and that barriers and facilitators to wider implementation will be identified.

## Design/Methods

### Design

A pragmatic three parallel group randomised controlled trial. People with Parkinson's in group A will be assessed and managed by a specialist MDT according to a care plan that is agreed amongst the professionals and with the patient and carer. Group B will additionally receive ongoing support for four months from a trained care assistant. Group C will receive normal care (no coordinated MDT care planning or ongoing support). Follow up will be for six months to determine the impact and relative cost-effectiveness of the two interventions. Qualitative interviews will be undertaken with providers (MDT members, care assistants), service commissioners, and patients and carers in groups A and B, to gain feedback about the acceptability of the interventions. The CONSORT diagram [42] summarises the design (Figure 1).

**Figure 1 F1:**
[figure not shown]
**CONSORT Flow Chart for SPIRiTT (Specialist Parkinson's Rehabilitation Team Trial)**.

### Setting

Contiguous communities around three district general hospitals (DGHs) in the county of Surrey, England. The study area contains urban, suburban and rural localities, and a broad mix of socio-economic and ethnic groups.

### Participants

People with Parkinson's (all stages of the disease) and live-in carers (where applicable).

### Recruitment

People with Parkinson's disease will be identified by a variety of means including: hospital clinics; general practitioners (GPs); Parkinson's UK contacts; PNS, community-based therapists; word of mouth. Research nurses from the Primary Care Research Network (PCRN) and the Dementia's and Neurodegenerative Diseases Research Network (DeNDRoN) will assist with the identification of people with Parkinson's through general practices and specialist Parkinson's hospital clinics respectively. Any interested person with Parkinson's will be given an information leaflet. Separate information will be provided for live-in carers (family, friends, paid carers living in the same household), where appropriate. People with Parkinson's and live-in carers will volunteer separately to take part in the study by contacting the research team, who will undertake an initial eligibility screen. This screening will include asking the patient to confirm that a doctor has told them that they have Parkinson's disease. Volunteers who meet the inclusion criteria (see below) will be sent full information about the trial, and a consent form, and an appointment will be made for a research nurse to make a home visit to collect baseline information. If a live-in carer does not want to take part in the research, the person with Parkinson's may still join the trial. However, carers will not be accepted if the person with Parkinson's does not want to participate.

### Inclusion criteria

People with Parkinson's (any stage of the disease) will be included if they: are 18 years of age or over; have a clinical diagnosis of Parkinson's disease; are living in the community (own home or minimally sheltered accommodation) with their own living areas; live in the county of Surrey (for reasons associated with the funding of the intervention); are able to read and write English in order to complete the self report questionnaires; express a commitment to participate over the duration of the study and provide written consent.

Live-in carers will be included if they: are 18 years of age, or over; are able to read and write English in order to complete the self report questionnaires; express a commitment to participate over the duration of the study and provide written consent.

### Consent and baseline data collection

Volunteers will be entered into the trial in blocks of thirty (geographically defined in order to reduce travel time and costs to participants' homes for the collection of the research data and delivery of the intervention). Research nurses will make a home visit to collect written consent(s) and record background information (age, gender, time since diagnosis, disease stage, co-morbidities, housing, caring arrangements, income and benefits, social support - Lubben Social Network Scale [43], cognitive function - mini mental state examination [44]). A baseline assessment will also be conducted using the outcome measures selected for the trial (see Table below). The intervention for each block of participants will start within two weeks of completion of baseline data collection.

### Exclusion criteria

Exclusion criteria will be checked by the research nurse at the baseline assessment. People with Parkinson's will be excluded if they: score at the most favourable end of all outcome scales at baseline, because the trial cannot demonstrate an improvement in these patients, and, in six months, has little likelihood of demonstrating reduction in any expected decline; score less than 24 on the mini mental state examination at baseline assessment [44], to ensure those recruited can follow instructions associated with the rehabilitation intervention; are already having a multidisciplinary package of care, or have had such care in the last six months; are taking part in another rehabilitation-based research study, or have taken part in such research in the last six months.

### Registration and randomisation

After consent and baseline data have been collected, eligible volunteers will be given a unique registration number by the project administrator and randomised to either: Group A - specialist rehabilitation, Group B - specialist rehabilitation and ongoing care assistant support, or Group C - usual care, control group. A separate randomisation sequence will be prepared by the study statistician prior to the commencement of the study for patients without live-in carers and for patients with live-in carers. In each instance, blocked randomisation will be used to formulate the sequence involving the three comparison groups. A non-computerised random number generator will create random permuted blocks of size three with an equal allocation ratio (with any of the six different group sequences being equally possible). The project administrator will inform: all participants of the group to which they have been randomised; the MDT of participants randomised to either of the treatment arms; the GPs of all participants about their involvement in the trial and the group to which they have been randomised. Since the project administrator will not be involved in the process of consenting volunteers into the study, and randomisation of eligible participants will be conducted in chronological order of study entry, no attempt will be made to conceal from the project administrator the next group to which the next patient would be allocated. However, only the project administrator and the study statistician will have access to each randomisation sequence.

### Interventions

#### Specialist rehabilitation intervention (Groups A and B)

A multidisciplinary team comprising two each of PNS, physiotherapist, occupational therapist, and speech and language therapist will be assembled from local professionals. They will work one day per week for the trial, and in other duties for the rest of the time. Team members will visit the homes of participants to deliver a specialist rehabilitation package, tailored to individual needs. In order to make the outcome from the trial comparable to that of the previous study set in a day hospital [10-12], a similar programme of specialist rehabilitation will be provided comprising an initial assessment, and the formation of an agreed care plan reflecting the needs, wishes and expectations of the person with Parkinson's and carers. A group education component in the day hospital trial cannot be replicated in the domiciliary setting. As a substitute, the MDT will provide participants with a folder containing 13 fact sheets produced by Parkinson's UK and the research team, covering various aspects of living with Parkinson's including: medications, physiotherapy exercises, foot care, diet and nutrition, speech and language, relaxation techniques, sleep and fatigue, continence and bowel care, rights and benefits and advice for carers.

The rehabilitation intervention will be coordinated by the PNS, and will involve specialist input from each professional, over a period of six weeks. The team will meet face-to-face four times in each six week cycle to discuss patient plans and progress, and communicate by email and telephone at other times. Two hospital consultants (neurologist and geriatrician), both with a special interest in movement disorders, can be called upon by the MDT for medication changes or advice. Referrals to a range of other professionals will be made as required, including community psychologist, social care manager, continence adviser, dietician and pharmacist. Overall three days of professional time (including travel and meeting time) is allowed for each person with Parkinson's in the trial, but some people may need more and others less than this. This input is largely equivalent to the 9-12 hours of individualised nursing and therapy input, and flexible access to other professionals, in the previous day hospital trial.

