#### Usual Care/Control (Group C)

Participants in the control group will continue to receive care as usual (no coordinated MDT care planning or ongoing support). When informed of their group allocation, they will be sent locally relevant and generic information about Parkinson's disease. This is a small enhancement on the service they are likely to be receiving. In order to measure the impact of the interventions, this information will also be given to the participants in Groups A and B. At the end of the trial, people in the control group will be offered an assessment by the MDT, with advice, and the fact sheets provided to groups A and B, but additional services cannot be guaranteed.

Cross contamination between groups will be minimal because patients will be individually recruited to the study, and receive treatments tailored to their specific needs. Moreover, the intervention and research assessments will take place in participants' homes which will be geographically dispersed over the catchment areas of three large district general hospitals.

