### Outcome measures

Participants in all groups will be assessed in their homes by a research nurse, according to the schedule used in the day hospital trial, at weeks 6 (after the rehabilitation intervention), 24 (four months after the end rehabilitation, coinciding with the end ongoing support for Group B), and 36 (for final follow up). Validated instruments which reflect the needs of participants (e.g. functional outcomes, quality of life) and service commissioners (e.g. service use), and which have been found sensitive in previous rehabilitation studies undertaken by the research team [10-13] have been selected to measure outcomes (Table 1).

**Table 1 T1:** Trial outcome measures and instruments: baseline, 6, 24 and 36 weeks

Participant	Outcome measure	Instrument
Person with Parkinson's	Parkinson's disability/general activities	Self Assessment Parkinson's Disease Disability Scale [46] (PRIMARY OUTCOME)
	
	Parkinson's specific	Parkinson's Disease Questionnaire [47]
		
		Non Motor Symptom Questionnaire [48]
	
	Mobility	Posture and gait items from the Unified Parkinson's Disease Rating Scale [49]
		
		Timed up and go [50]
	
	Falls	Self report
	
	Speech	Single speech item from the Unified Parkinson's Disease Rating Scale [49]
		
		Abridged Emerson and Enderby Screening Assessment Rating Scale [51]
		
		Frenchay Dysarthria Summary [52]
		
		Speech self report questionnaire [10-12]
	
	Pain	Visual analogue scale [53]
	
	Generic health related quality of life/QALYs	Euro Qol 5D, with utility index for calculation of quality adjusted life years (QALYs) [54]
	
	Self efficacy	Self efficacy scale [55]
	
	Health and social care utilisation	Customised proforma and patient records

Live-in carer	Carer strain	Modified caregiver strain index [56] (PRIMARY OUTCOME)
	
	General health	General health questionnaire - 12 [57]

Both	Activities of daily living	Barthel ADL index [58]
	
	Social activities	Frenchay Activities index [59]
	
	Psychological wellbeing	Hospital Anxiety and Depression Scale [60]
		
		Yale single item depression screening tool [61]
	
	Generic health related quality of life	Short form - 36 Health Survey [62]

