The instrument battery was developed and piloted in collaboration with patient and carer representatives. It takes about one hour to complete, and was not been found too onerous. Research nurses will assist patients with completion of questionnaires. Carers will be asked to self complete the questionnaires that apply to them. All questionnaires will be checked for completeness before the research nurse leaves the participant's home. Data will be entered by the research nurse shortly after collection, and any queries referred back to the participant by telephone. A further check on data (completeness and entry) will be undertaken by the research manager when forms are returned to the office by the research nurse, and missing items or other issues will be resolved. Patient and carer outcomes will be analysed separately.

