### Blinding

The research administrator will not disclose group allocation to the research nurses who undertake assessments, and participants will be asked not to discuss aspects of the trial and treatments with them. However, it is recognised that blinding of the research nurses may be compromised in trials of this nature. As a check on blinding, research nurses will be asked to guess participants' groups at the end of the trial. For data analysis, the group identifiers will not be disclosed to the statistician.

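### A fact-sheet folder given only to Groups A and B during follow-up is one modest, cheaply reduced route to unblinding the nurse who assesses at home, because the stated blinding measures cover only communication

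*Protocol article*

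**What the plan says.** Under the specialist rehabilitation intervention for Groups A and B, treatment is given at home: "Team members will visit the homes of participants to deliver a specialist rehabilitation package, tailored to individual needs". To replace the group education of the earlier day hospital trial, "the MDT will provide participants with a folder containing 13 fact sheets produced by Parkinson's UK and the research team". The listed topics include physiotherapy exercises, speech and language, relaxation and advice for carers.

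The Usual Care/Control section gives Group C the same sheets later: "At the end of the trial, people in the control group will be offered an assessment by the MDT, with advice, and the fact sheets". A separate set of locally relevant, generic information is sent to controls when they learn their allocation, and "this information will also be given to the participants in Groups A and B". That item is common to all arms. The folder is not.

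Under Outcome measures, "Participants in all groups will be assessed in their homes by a research nurse", at weeks 6, 24 and 36. The same section adds: "Research nurses will assist patients with completion of questionnaires". Carers complete their own questionnaires.

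The Blinding section has two preventive measures. The administrator does not disclose allocation to the nurses, and "participants will be asked not to discuss aspects of the trial and treatments with them". It then concedes that nurse blinding may be compromised in a trial of this kind, and plans for nurses to guess the allocations when the trial ends.

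**The concern.** Both preventive measures work by limiting what people say. Neither addresses an object that belongs to the treated arms during follow-up and may be lying in the room where the assessment is made. A nurse who sees the folder may infer that the participant is in Group A or B.

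Such knowledge matters most where the nurse exercises judgement or runs the test: the posture, gait and speech items of the Unified Parkinson's Disease Rating Scale, and timed up and go. It could also colour the help given with patient questionnaires, which include the self-assessed disability scale that is the patient primary outcome. The comparisons exposed are A against C and B against C at weeks 24 and 36, and A and B together against C at week 6. If expectation favoured treatment, the drift would be towards the treated groups.

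**Working it through.** The plan gives no figure on this point, so the check consists of setting its statements side by side.

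1. **Who holds the folder, and when.** The MDT provides it within the home-delivered package to Groups A and B. Group C is offered the sheets only at the end of the trial. At weeks 6, 24 and 36 the folder should therefore be in the possession of A and B participants and not of C participants.
2. **Whether the common information pack evens this out.** It does not. It is a separate item that all three groups receive; A and B have the folder as well.
3. **Where the nurse works.** All three follow-up assessments are made at home. Baseline is also a home visit, but it precedes randomisation, so the folder cannot reveal anything then.
4. **What the safeguards cover.** Administrator non-disclosure covers information from the trial office. The request to participants covers conversation. Neither covers visible materials. The guess at the end of the trial may detect unblinding, but it comes after the outcomes are collected and prevents nothing.
5. **What the folder can reveal.** It separates A or B from C. It does not separate A from B, so the A against B comparison is not exposed by this route.
6. **Which outcomes are exposed, in order.**
   - Nurse-rated posture, gait and speech, and timed up and go: directly.
   - Patient questionnaires, including the primary disability scale: indirectly, because they are self-report with nurse assistance.
   - Carer strain, the carer primary outcome: largely unexposed, because carers self-complete.

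Two links are inferences. That the folder stays in the home follows closely from its being given to people treated at home, but it is not stated. That it is left where a nurse would see it is not stated at all.

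**The case against.** The strongest reply has four parts.

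- **The risk is conceded and checked.** The Blinding section admits that blinding may fail, and the guess check would register unblinding from any source. This stands and lowers the weight of the point, although neither the concession nor the check prevents anything.
- **An article condenses the full protocol.** A request to put materials away could sit in a nurse manual or the full protocol. This also stands: the article contains no contradiction here. The point is only that the measures it does describe stop at communication.
- **The folder is not the only cue, nor an unmistakable one.** Acceptability interviews with A and B participants take place during the 24-week assessment, service use is self-reported at each assessment, and the MDT's home visits assess aids and adaptations. The sheets come partly from Parkinson's UK, recruitment runs partly through Parkinson's UK contacts, and all arms receive written information, so leaflets in a home need not identify the arm. This stands.
- **The patient primary outcome is self-assessed.** Any influence of the nurse on it is indirect. This stands.

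A reader might go further and infer a known inflation of type I error. Suppose the folder is noticed in 30% to 60% of treated homes and knowing the arm shifts a score by 0.1 to 0.2 SD. The mean bias is then 0.30 × 0.1 = 0.03 SD to 0.60 × 0.2 = 0.12 SD. With 90 × 0.90 = 81 analysed per group, the standard error is √(1/81 + 1/81) = 0.157 SD, and a nominal 5% t test rejects a true null in 5.4% to 11.8% of cases. For 162 against 81 at week 6, the standard error is √(1/162 + 1/81) = 0.136 SD and the range is 5.6% to 14.2%. The arithmetic is right, but the documents do not support the reading. Neither the noticing rate nor the shift has any source in them, and the calculation credits all unblinding to the folder although the other cues would remain.

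**Conclusion.** The point holds as a minor weakness. Only Groups A and B have the folder during follow-up, follow-up is at home with a nurse meant to be blind, and the stated preventive measures do not extend to visible materials. Seeing the folder could suggest A or B rather than C at weeks 6, 24 and 36.

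The size of any resulting bias cannot be derived from the documents. The conclusion assumes that the folder is kept at home and is sometimes on view, and that a nurse would recognise it as treatment material. It does not support a claim that blinding will fail because of the folder, or that either primary result is invalid.

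**What to change.** Extend the request in the Blinding section from conversation to materials, and put it in every follow-up appointment letter in identical wording for all three groups: *please put any written Parkinson's or study materials out of sight before the nurse arrives.* The wording must be neutral. A sentence that mentioned a care plan or exercise sheets would not fit Group C. An outwardly identical folder for controls is largely redundant once materials are put away.

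The cost is one sentence in the letter, with no extra staff, visits or participants and no change to treatment. It reduces unblinding by this route but cannot remove it: some participants will forget, and the other cues are untouched.
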